## **Methods**

### **Design**

STOP GAP is a multicentre, parallel group, observer-blind, randomised controlled trial (Figure 1). This is a superiority trial, with prednisolone as the control intervention. The decision to power the STOP GAP trial on the basis of superiority was made as (i) ciclosporin is considerably more expensive than prednisolone (which means that it would need to be considerably better than prednisolone to warrant a change in clinical practice); (ii) case series and clinical experience give the impression that ciclosporin may gain control more quickly, and have a side-effect profile that is more suitable for long-term therapy; and (iii) pragmatically, for a rare condition such as PG, this was felt to be the best approach as an equivalence trial would require a much larger trial that could only be delivered internationally, which was beyond the scope of our funding.

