**Figure 1 F1:**
[figure not shown]
Flow chart of trial recruitment.

The study aims to recruit 140 patients with PG over a 4-year period. Participants are randomised using a ratio of 1:1 to receive either oral prednisolone (0.75 mg/kg/day) or oral ciclosporin (4 mg/kg/day). Patients who initially require topical therapy are asked to enter a parallel observational study, the purpose of which is to provide an estimate of treatment response to topical therapy in a well defined prospective case series, and also to enhance recruitment by allowing those who fail on topical therapy to enter the main study (Figure 1).

Follow-up is continued until the lesion has healed, or for a maximum of 6 months (whichever is sooner).

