### **Interventions**

Participants are randomised to receive either oral prednisolone 0.75 mg/kg/day or ciclosporin (Neoral) 4 mg/kg/day (in two divided doses), up to a ceiling dose of 75 mg/day prednisolone and 400 mg/day ciclosporin. The dose of study drug can be adjusted (up or down) by the investigator according to response after the week 2 visit. If possible the dose of study drug should not be altered for the first 2 weeks of the study.

The use of a double dummy design was not felt to be appropriate for this study as the side effect profile, monitoring requirements and dosing regimen for the compared drugs is very different, making such a design both costly and possibly ineffective. As a result the trial team opted to ensure blinded outcome assessment of the primary outcome (using digital images) and secure allocation concealment. Participants are prescribed study medication from standard pharmacy supplies at each recruiting hospital.

Participants of the RCT should not use any topical therapy (for example, corticosteroids or calcineurin inhibitors) after randomisation. If topical therapy has been prescribed while the participant is waiting to enter the study it should be stopped when the participant enters the RCT. All other concomitant medications should continue as per normal care. The use of live vaccines is not permitted during the intervention phase of the trial and clinicians will be advised not to start Rosuvastatin (Crestor) on any patients receiving ciclosporin as it is contraindicated. Participants are asked to assess how well they adhered to study drug at week 6 and at 6 months (or time of healing).

Participants in the observational arm of the study receive whichever topical therapy is prescribed as per normal care at the recruiting hospital (this is most likely to be clobetasol propionate (Dermovate) or tacrolimus (Protopic 0.1% or 0.03%) as there is reasonable evidence to support the use of both of these treatments [10,11].

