### **Randomisation and blinding (masking)**

The randomisation schedule has been created by the Nottingham Clinical Trials Unit data manager using the ralloc Strata (College Station, TX, USA) add-on. Participants are randomised to treatment allocation using a computer-generated pseudorandom list using permuted blocks of randomly varying size between 2 and 6. Randomisation is stratified by lesion size (≥20 cm^2^ vs lesions <20 cm^2^) and presence or absence of underlying systemic disease. The randomisation schedule will be concealed until interventions are all assigned and recruitment, data collection, data cleaning and analysis are complete.

This is an observer-blind study. The primary outcome (velocity of healing) is assessed on the basis of digital images of the target lesion in order to protect against detection bias. The digital images will be assessed by two assessors who are blinded to treatment allocation, using patient number as the identifier. The images will also be used to assess global improvement in disease and the PG inflammation scale (if possible, depending on the quality of the images).

Both clinicians and participants know their treatment allocation and so no special measures are required to allow for breaking of treatment codes. However, treatment allocation will not be revealed to the recruiting physician until participants’ details and key stratification variables have been irrevocably entered by the physician onto the web-based randomisation site.

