### **Secondary outcomes**

Secondary outcomes include the following: (1) time to healing assessed by participants (estimated to the nearest week) based on the time at which sterile dressings are no longer required for the wound. Healing is confirmed by the clinician, and documented using digital photography at the first opportunity. Time to healing is important clinically as it will be used to confirm the primary outcome as a useful surrogate measure. It also gives an indication of duration of treatment, which therefore provides information on cumulative drug toxicity. (2) PG specific global assessment of efficacy (derived from a study by Foss *et al.*[14]) as assessed by the clinician and the patient at 2 weeks, 6 weeks and at 6 months (or healed). This will also be assessed on the digital images by an independent assessor. (3) Inflammation assessment scale. This is a combination scale including erythema, border elevation and exudate (based on a scale reported by Foss *et al.*[14]). The inflammation assessment scale is recorded by the clinician and the participant at baseline, 2 weeks, 6 weeks and when the ulcer has healed (maximum 6 months). This will also be assessed on the digital images by an independent assessor. (4) Self-reported pain. Each day for the first 6 weeks of the trial participants report the severity of the pain in a study diary (none, mild, moderate, severe or extreme), and whether or not painkillers were taken. (5) Health-related quality of life assessed at baseline, 6 weeks and 6 months (or healed), using validated questionnaires: Dermatology Life Quality Index [15] and the EQ-5day [16]. (6) Time to recurrence assessed at the end of the trial. A recurrence is defined as the occurrence of a further episode of PG (at any site) that appears after the target lesion has been confirmed as being healed by a physician (or nurse). Self-reported healing that has not been confirmed by a medical professional, and which subsequently recurs, will not be classed as a recurrence and handled as a continuation of the initial episode. (7) Number of treatment failures. Treatment failures are defined as being participants who withdraw (or are withdrawn) from their randomized treatment because of treatment intolerance or worsening of the PG, or those who continue to have any unhealed ulcers after 6 months of follow-up. (8) Adverse reactions to study medications. Adverse events that are classed as possibly, probably or definitely relating to the study medication. (9) Cost effectiveness of the compared treatments.

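### The only stated safety outcome counts events attributed to the drug in a trial where the allocation is known, so the safety comparison is open to differential attribution

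*Protocol article*

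**What the plan says.** Item 8 of the protocol article's Secondary outcomes is adverse reactions to study medication, defined as "Adverse events that are classed as possibly, probably or definitely relating to the study medication". No other safety outcome is listed, although Objectives names safety as a secondary objective. The definition does not say who does the classing.

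On blinding, the Randomisation and blinding section states: "Both clinicians and participants know their treatment allocation". The Interventions section explains that a double dummy was rejected, partly because the drugs differ so much in side effects and monitoring, and continues: "As a result the trial team opted to ensure blinded outcome assessment of the primary outcome (using digital images) and secure allocation concealment". The blinding section extends blinded image assessment to global improvement and, where image quality allows, inflammation. Adverse events are not covered.

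On observation time, the Design section says: "Follow-up is continued until the lesion has healed, or for a maximum of 6 months (whichever is sooner". Secondary outcomes says of time to healing: "It also gives an indication of duration of treatment, which therefore provides information on cumulative drug toxicity". The same section lists "Time to recurrence assessed at the end of the trial", which requires some information after healing.

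Design also records a prior view of the drugs: "case series and clinical experience give the impression that ciclosporin may gain control more quickly, and have a side-effect profile that is more suitable for" (the sentence goes on to name prolonged treatment).

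**The concern.** An outcome made of attributed events depends on two things: whether an event happened, and whether someone judged it drug-related. Randomisation protects the first. It does not protect the second when the person judging may know the drug. Because the two drugs have different recognised side effects, the same event could plausibly be counted in one arm and left out in the other. The trial guards its primary outcome against this kind of judgement by blinded reading of images. Its safety outcome has no comparable protection in the text.

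The second part concerns time at risk. Healing is what the treatments are meant to influence, and general follow-up stops at healing. If one drug heals ulcers sooner, its patients are watched for less time and would show fewer events at the same weekly rate.

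At stake is a stated secondary objective. Side-effect profile is also part of one of the three reasons given for powering the trial on superiority. The primary outcome is not affected.

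**Working it through.** **Inputs.** The Sample size section gives 140 patients, 1:1, so 140/2 = 70 per arm. That total reproduces: 63 per arm for 0.5 SD, 5% two-sided, 80% power (normal approximation), and 126/0.9 = 140. It concerns velocity of healing and is not in dispute. The article gives no figure for the safety outcome, and no event, attribution or healing rates. Everything below is therefore an illustration under assumed values.

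**1. Attribution.** Let r be the true risk of an adverse event, equal in both arms, and a1 and a2 the shares of patients with an event whose event is classed as related. The observed proportions are r·a1 and r·a2, and the spurious difference is r(a1 − a2). The chance of p<0.05 is Φ[(d − 1.96·SE0)/SE1], where d is the difference, SE0 the pooled and SE1 the unpooled standard error. The opposite tail adds less than half a percentage point.

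With r = 60% and n = 70 per arm:

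- Equal attribution: d = 0, no spurious difference (5% chance of p<0.05 by design).
- 80% v 70%: 0.60×0.80 = 48% and 0.60×0.70 = 42%, d = 0.06. SE0 = √(2×0.45×0.55/70) = 0.0841 and SE1 = √[(0.48×0.52 + 0.42×0.58)/70] = 0.0839. (0.06 − 1.96×0.0841)/0.0839 = −1.25, so about 10.6%.
- 80% v 60%: 48% and 0.60×0.60 = 36%, d = 0.12. SE0 = √(2×0.42×0.58/70) = 0.0834 and SE1 = √[(0.48×0.52 + 0.36×0.64)/70] = 0.0828. (0.12 − 1.96×0.0834)/0.0828 = −0.53, so about 30%.

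Varying r from 50% to 70% moves these chances to 8.8%–12.9% and 23.5%–38.0%. With 63 per arm and r = 60% they are 9.9% and 27.4%.

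**2. Observation time.** Assume exponential healing with weekly hazard h, follow-up ending at healing or 26 weeks. Mean follow-up is (1 − e^(−26h))/h. If a proportion p of the slower arm heals by 26 weeks, h = −ln(1 − p)/26. The other arm has hazard HR·h.

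| Healing HR | Mean weeks, p = 40% (ratio to slower arm) | Mean weeks, p = 60% (ratio to slower arm) |
|---|---|---|
| 1.0 | 20.4 (1.00) | 17.0 (1.00) |
| 1.25 | 19.2 (0.94) | 15.5 (0.91) |
| 1.5 | 18.2 (0.89) | 14.1 (0.83) |
| 2.0 | 16.3 (0.80) | 11.9 (0.70) |

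The effect on the proportion of patients with any event is smaller. With event hazard λ per week it is λ/(λ+h)·[1 − e^(−26(λ+h))]. For p = 50%, HR = 1.5 and λ = 0.05 in both arms, this gives 56.3% v 50.2%, a ratio of 50.2/56.3 = 0.89, against a mean follow-up ratio of 16.2/18.8 = 0.86.

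**The case against.** The article summarises a fuller protocol. Who judges causality, how all events are tabulated and whether rates are used are ordinarily left to that protocol or the analysis plan. Nothing in the article says that unattributed or serious events will go unreported, and an independent data monitoring committee oversees safety. The definition includes events that are only possibly related, a low threshold that limits how many are excluded.

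This stands as far as it goes: silence on those details is not a fault. But the restriction to attributed events is a stated choice of outcome, and that choice is the point here.

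Four stronger readings are tempting, and the text does not support them:

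- **That unblinded clinicians do the classing.** This is a reasonable inference, but the article names no classifier.
- **That the comparison is biased.** Bias requires attribution to differ between arms. With equal attribution no spurious difference arises. The prior impression favouring ciclosporin suggests a possible direction, but does not show that attribution followed it.
- **That exposure is unequal.** This follows only if healing times differ.
- **That safety observation plainly stops at healing.** Recurrence assessed at the end of the trial implies some later contact, so the safety window after healing is unclear.

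There is also a fair case for counting reactions over the treatment course. If treatment stops around healing, less drug exposure through faster healing is a real benefit, and a rate per person-time would remove it. The article itself links healing time to treatment duration and cumulative toxicity. This weakens the observation-time part and is why person-time rates belong as a supplement.

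**Conclusion.** The point holds as a susceptibility in the chosen safety outcome. Known allocation, very different side-effect profiles, an outcome limited to attributed events and no described blinded causality review together leave the between-drug comparison open to differential attribution.

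Its size cannot be fixed from the documents. At an assumed 60% true risk in both arms and 70 per arm, the spurious difference is 0, 6 or 12 percentage points for attribution gaps of 0, 10 or 20 points, with about a 5%, 11% or 30% chance of p<0.05.

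The observation-time part is secondary and conditional. Assuming 40–60% of the slower arm heals by 26 weeks, the ratio of mean follow-up runs from 1.00 at a healing hazard ratio of 1.0 to 0.80–0.70 at 2.0. A secondary outcome is affected, and the repair can be made before analysis.

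**What to change.** Make the main safety comparison all recorded adverse events and all serious adverse events by randomised arm, regardless of attribution. Keep events classed as related as a supportive table, with a sentence saying who judged causality and whether that person knew the allocation. Give event rates per person-time of observation alongside the per-patient proportions, so that the experience over the treatment course and the rate can both be read.

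The cost is mainly extra tables. Events have to be recorded before they can be classified, so little or no new data should be needed, and person-time can use the follow-up already planned. The downside is that background events unrelated to either drug dilute drug-specific differences, which is a reason to keep the attributed table. A common 6-month safety window is not needed for this repair: it could require new follow-up after healing, and it would add time off treatment and so answer a different question.

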### **Sample size**

A total of 140 patients (randomised 1:1 to prednisolone or ciclosporin) will give the study at least 80% power at a 5% level of significance using a two-sided two-sample *t* test to detect a difference in means of 0.5 SDs of the primary outcome of velocity of healing at 6 weeks. The velocity of healing at 6 weeks is defined as the percentage change in surface area (measured by planimetry using digital photographs) over baseline of the target lesion. This sample size allows for an approximate 10% loss to follow-up at 6 weeks. These calculations were performed using Nquery 6.0.2 on Windows XP (Microsoft, Redmond, WA, USA).

### **Statistical analysis**

The primary analysis will be according to the intention to treat principle, and will adjust for known prognostic baseline covariates. There are no formal planned interim analyses, but progress reports on all data issues are presented to a Data Monitoring Committee (DMC).

The primary outcome is to be assessed at 6 weeks, which reduces the likelihood of having missing data for this outcome. If digital images are not available for any participants, then the physical length and width measurements recorded by the clinician will be used in place of the computer generated planimetry measurements. If neither a digital image, nor physical measurements are available at 6 weeks, multiple imputation will be used using the assumption that the data are missing at random.

All primary outcome data will be double data entered and 10% of other data will be entered twice and checked for errors.

Categorical variables will be summarised with the number and proportion of participants falling in each category. Continuous variables will be summarised using the number available, number missing, mean and standard deviation (SD), or median, 25th and 75th quartiles, and minimum and maximum values as appropriate.

Differences between treatment groups for the primary and secondary outcomes will be assessed using Student’s *t* test. Linear regression models, adjusting for baseline covariates, will be used to compare the treatment groups at 6 weeks for the primary outcome, and any other continuous secondary outcomes that fit the assumptions. Cox regression models, adjusting for baseline covariates, will be used to compare the treatment groups in the analysis of the time to healing of the target lesion and the time to recurrence. Proportional odds models, adjusting for baseline covariates, will be used to analyse the categorical secondary outcomes, including global assessment of improvement and the inflammation assessment scale. The self-reported pain and the EQ-5D score will be summarised by the area under the curve (AUC), using Generalized linear models with the appropriate distribution. Patients are required to have the data recorded at the initial timepoint, and at the 6 week timepoint (for the 6 week analyses) or the final visit (for the final visit analyses), so only patients with at least the first observation and the last observation for the self-reported pain data, or those with both timepoints for the EQ-5D data, will be analysed in the first instance. Sensitivity analyses will be carried out for the self-reported pain outcome using the ‘last value carried forward’ method for patients who have missing interim data.

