### **Primary outcome**

The primary outcome is velocity of healing at 6 weeks. This will be captured for a single target lesion per patient and measured using digital photography and Verge Videometry VEV MD (Vista Medical, Winnipeg, Canada) computerised planimetry [12]. If multiple lesions are present, the target lesion should be the lesion that is most able to be photographed on a single plane (that is, not around the curvature of a limb). Digital images will be taken at baseline, 6 weeks and when the ulcer has healed (maximum 6 months). In addition, maximum longitudinal length and maximum perpendicular length will be measured in order to provide some measure of improvement in case of difficulties with the digital images, or if the lesion extends around the curvature of a limb. This will be converted to approximate area by the formula: length × width × 0.785, which approximates to an ellipse for the purpose of randomisation and analysis.

Velocity of healing at 6 weeks was chosen as the primary outcome as it is unlikely to be compromised by the single blind nature of the study, and does not require lengthy follow-up, thus minimising the possibility of missing data. Previous work in patients with venous leg ulcers suggests that velocity of healing is a good surrogate for subsequent healing [13].

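### The follow-up, imaging and imputation rules are not reconciled for target lesions that heal before week 6, so an outcome known to be complete healing can be multiply imputed

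*Protocol article*

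**What the plan says.** Four places in the Protocol article bear on this.

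- **Design** (text below Figure 1): "Follow-up is continued until the lesion has healed, or for a maximum of 6 months (whichever is sooner"). No minimum of six weeks is stated.
- **Primary outcome**: "Digital images will be taken at baseline, 6 weeks and when the ulcer has healed (maximum 6 months"). Week 6 is a timepoint of its own, and nothing says whether it still applies after earlier healing.
- **Sample size**, which also defines the endpoint: "The velocity of healing at 6 weeks is defined as the percentage change in surface area" of the target lesion relative to baseline. A healed lesion therefore has a determinate value, a 100% reduction.
- **Statistical analysis**: clinician length and width replace a missing image. Beyond that, "If neither a digital image, nor physical measurements are available at 6 weeks, multiple imputation will be used", with the data assumed missing at random. Confirmed healing is not mentioned.

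The Secondary outcomes section adds that a clinician confirms healing and that it is photographed as soon as possible. That confirmation is not tied to week 6.

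**The concern.** Take a participant whose target lesion is confirmed healed at week 4. The Design section allows follow-up to end there. If no week-6 image or ruler measurement is then taken, the Statistical analysis section sends that participant to multiple imputation, although the week-6 area is already known.

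Missing at random is a poor assumption for this group, because the record is absent precisely because the area reached zero. An imputation model informed mainly by participants still ulcerated at week 6 would replace complete responders with partial ones.

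The primary objective is speed of response. The Design section justifies superiority partly by the impression that ciclosporin may gain control faster. Unequal early healing is therefore something the trial's own hypothesis makes plausible, and in that case the rule works against the faster drug.

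**Working it through.** **1. The plan's own figure.** Inputs from the Sample size section:
- total and allocation: 140 participants, 1:1;
- power and level: 80% or more at two-sided 5%, comparing two means;
- effect size: "to detect a difference in means of 0.5 SDs of the primary outcome of velocity of healing at 6 weeks";
- dropout: about 10% by week 6.

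n per arm = 2(1.960 + 0.842)² / 0.5² = 62.8, rounded up to 63, so 126 in total. Then 126 / 0.90 = 140. The stated size reproduces. The exact *t*-test version gives 64 per arm, 128 in total and 143 after inflation, which is within 3%. Nothing below changes the 140.

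**2. The rules side by side, for healing at week 4.**

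| Section | Consequence |
|---|---|
| Design | Follow-up may end at week 4 |
| Primary outcome | A week-6 image is scheduled, and a healing image is taken |
| Secondary outcomes | Healing is confirmed by a clinician and photographed |
| Statistical analysis | With no week-6 image or measurement, the outcome is imputed |

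The sections do not settle whether this participant has a week-6 record, or whether the healing image counts as one.

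**3. Illustrative size.** The article gives no early-healing rate and no SD, so everything in this step is assumed:
- the latent percentage reduction is normal with SD 40 points, capped at 100 (healed);
- 63 participants per arm;
- every early healer lacks week-6 data;
- imputation is within arm from non-healers, approximated by the difference between non-healer means.

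For a healed share h, with z the (1 − h) normal quantile and φ the normal density at z:
- true arm mean = 100 − SD × [z(1 − h) + φ];
- non-healer mean = 100 − SD × [z + φ/(1 − h)].

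Worked example, 15% v 5% healed:
- h = 0.15: z = 1.036, φ = 0.233, true mean 55.43, non-healer mean 47.57.
- h = 0.05: z = 1.645, φ = 0.103, true mean 33.37, non-healer mean 29.86.
- True difference 55.43 − 33.37 = 22.06. Imputed difference 47.57 − 29.86 = 17.71. Shrinkage 1 − 17.71/22.06 = 20%.

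Simulation (4,000 trials per scenario) agrees and adds power:

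| Healed early | True difference | Imputed difference | Shrinkage | Power, true v imputed |
|---|---|---|---|---|
| 10% v 5% | 13.4 | 11.0 | 18% | 52% v 40% |
| 15% v 5% | 22.1 | 17.8 | 20% | 92% v 78% |
| 20% v 10% | 15.1 | 11.4 | 24% | 68% v 45% |
| 25% v 10% | 20.1 | 15.1 | 25% | 90% v 67% |
| 30% v 15% | 15.9 | 11.7 | 27% | 77% v 48% |

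With equal rates (5% v 5%, 20% v 20%) the difference is unbiased and the rejection rate is about 5%.

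Both differences are proportional to the SD. With the healed shares held fixed, the SD therefore changes the points but not the percentage shrinkage.

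**4. Extreme case.** Suppose non-healers have the same mean reduction m in both arms, so that only the healed share differs. The true difference is (h₁ − h₀)(100 − m), and imputation takes it to about 0. For 15% v 5%, m = 20 gives 0.10 × 80 = 8 points and m = 40 gives 0.10 × 60 = 6 points. At an assumed SD of 50 that is 0.16 or 0.12 SD, against the design effect of 0.5 SD.

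**The case against.** The strongest reply is that healing brings the final visit forward but does not cancel week 6.

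- The image schedule exempts nobody. For adherence, global assessment and quality of life, the alternative of healing is attached to the six-month visit, with week 6 listed separately. Pain diaries run for the first six weeks.
- The Design sentence cannot mean that all contact ends at healing, because recurrence after confirmed healing is assessed at the end of the trial.
- No scheduled assessment falls between weeks 2 and 6. Healing reported at week 4 might well be confirmed and photographed at week 6, which would supply the outcome directly.
- Imputation is a last resort, and a sensible analyst would score a healed lesion as zero. The article summarises a longer protocol that may say so.

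Much of this stands. A reader might infer that every early healer is lost at healing and imputed as a matter of course. The documents do not support that, because the scheduled week-6 image and the healing photograph mean some or all of them may have usable data. A reader might also infer that imputation uses baseline covariates only, so that missing at random must fail. The imputation model is not stated, and week-2 assessments or healing status in it would reduce the shrinkage. Nor does the defect extend to the secondary outcomes. The imputation rule is given for the primary outcome, and pain and EQ-5D are handled by requiring recorded timepoints.

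The reply does not remove the conflict in the text. The article does not leave missing primary data to another document. It states a rule, keyed to what is available at six weeks, and that rule covers a lesion already known to be healed.

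**Conclusion.** The point holds as an unreconciled set of rules on the primary endpoint. Followed literally, they permit a known 100% reduction to be imputed. They do not show that this will happen, or to how many participants.

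If early-healing rates differ between arms, the bias is towards a smaller difference. It is about 18% to 27% of the true difference, with a power loss of about 12 to 29 percentage points, under the assumptions in step 3. If rates are equal, the difference is unbiased. A reader might infer from step 4 that the early-healing contribution is lost entirely. That needs identical non-healer means in both arms and no week-6 data for any early healer, and nothing in the article supports either.

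The magnitude is illustrative throughout. The correction is still worth making before treatment allocation is revealed, because it concerns the primary analysis. It does not mean that the design is unsound or that 140 is wrong.

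**What to change.** Add to the primary-outcome analysis rules: a target lesion with clinician-confirmed healing by week 6 and no recorded reopening by then is scored as area 0 (100% reduction) in the primary analysis. Multiple imputation is restricted to participants not known to be healed.

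The Design, Primary outcome and Statistical analysis sections should then be reconciled, so that it is clear whether the week-6 assessment takes place after earlier healing and whether the healing image can serve as the week-6 record.

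The cost is one sentence plus that cross-check. Clinician confirmation and the healing photograph are already collected, so the scoring rule needs no new data and no change to the sample size. It does rely on a reopening before week 6 being recorded.

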### **Cost effectiveness**

Costs of the compared treatments will be assessed from the perspective of the health service, using resources such as inpatient stays, outpatient attendances, primary care appointments (at surgery), home visits by GP, district nurse visits and PG-related treatment costs. Cost effectiveness will be presented as the cost per healed ulcer at 6 months.

Health related quality of life will be estimated from responses to the Dermatology Life Quality Index. Quality-adjusted life years will be assessed from responses to the EQ-5D questionnaire, and the incremental cost per quality-adjusted life years gained will be presented for the compared treatments. Health state utilities will be calculated using UK population tariffs. Estimates of resource use (from medical records and patient diaries) will be combined with unit costs, to derive total costs. Unit costs will be based on study specific estimates and data from standard sources. Point estimates of mean incremental costs, QALYs, cost per QALY and cost per resolved episode at 6 months will be reported.

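### The final-visit EQ-5D AUC ends at healing or 6 months, so its length depends on the outcome; left unstandardised, it counts against the faster-healing arm

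*Protocol article*

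**What the plan says.** Four places in the protocol article bear on this.

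- Design (text below Figure 1): "Follow-up is continued until the lesion has healed, or for a maximum of 6 months (whichever is sooner".
- Secondary outcomes, item 5: "Health-related quality of life assessed at baseline, 6 weeks and 6 months (or healed), using validated questionnaires". No EQ-5D is scheduled after healing.
- Statistical analysis: "The self-reported pain and the EQ-5D score will be summarised by the area under the curve (AUC". Participants need a baseline value and one "at the 6 week timepoint (for the 6 week analyses) or the final visit (for the final visit analyses". For this instrument, "or those with both timepoints for the EQ-5D data, will be analysed in the first instance".
- Cost effectiveness: "Quality-adjusted life years will be assessed from responses to the EQ-5D questionnaire", and "Point estimates of mean incremental costs, QALYs, cost per QALY and cost per resolved episode at 6 months will be reported".

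For the final-visit EQ-5D AUC the article gives no common horizon, no rule for utility after healing and no division by time. Its carry-forward rule covers only missing interim pain data.

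**The concern.** Read together, the first three statements give each participant a different AUC window, and healing sets its length. Someone healed at week 10 contributes about 10 weeks of utility; someone never healed contributes 26. Treatment can change the window through the very effect under test, so the two arms are not summed over the same time. As long as utilities are positive, the raw sum is larger for those who stay ulcerated longer.

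The same EQ-5D responses feed the QALYs. The Design section justifies a superiority trial partly by the higher price of ciclosporin, so a quality-of-life or QALY difference with the wrong sign would mislead on a question the trial means to inform.

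**Working it through.** **Inputs.** From the article: EQ-5D at baseline, week 6 and the final visit; final visit at healing or at 6 months (26 weeks). The article gives no EQ-5D, AUC or QALY figure, so there is nothing to reproduce on this point. All utilities, healing times and healing proportions below are assumptions.

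**Direction.** Let utility rise in a straight line from u0 at baseline to uh at healing in week T.

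- Stopped at healing: AUC = (u0 + uh)/2 × T/52 years. This increases with T whenever u0 + uh is positive, so slower healing scores higher.
- Over 26 weeks, with uh carried forward: AUC = (u0 + uh)/2 × T/52 + uh × (26 − T)/52. This decreases with T whenever uh exceeds u0, so faster healing scores higher.

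With u0 = 0.5 and uh = 0.8:

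- T = 12: stopped, 0.65 × 12/52 = 0.150; over 26 weeks, 0.150 + 0.8 × 14/52 = 0.365.
- T = 20: stopped, 0.65 × 20/52 = 0.250; over 26 weeks, 0.250 + 0.8 × 6/52 = 0.342.
- Fast minus slow: −0.100 stopped, +0.023 over 26 weeks.

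**Healed against unhealed, trapezoid on weeks 0, 6 and final.**

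- Healed at week 10 (0.50, 0.70, 0.85): (0.60 × 6 + 0.775 × 4)/52 = 0.129. Adding 0.85 × 16/52 gives 0.390 over 26 weeks.
- Unhealed (0.50, 0.55, 0.60): (0.525 × 6 + 0.575 × 20)/52 = 0.282.
- Healed at week 12 (0.50, 0.65, 0.85): (0.575 × 6 + 0.75 × 6)/52 = 0.153. Adding 0.85 × 14/52 gives 0.382.

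For arms with 60% and 45% healed at week 12, the difference is 0.15 × (0.153 − 0.282) = −0.019 stopped and 0.15 × (0.382 − 0.282) = +0.015 over 26 weeks. With 70% and 50% healed, the multiplier is 0.20 and the results are −0.026 and +0.020.

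**Arm level, exponential healing times (simulated), faster minus slower arm, in QALYs.**

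| u0 to uh | Median weeks to healing | Stopped at healing | Common 26 weeks |
|---|---|---|---|
| 0.3 to 0.7 | 12 v 16 | −0.0157 | +0.0133 |
| 0.3 to 0.7 | 12 v 20 | −0.0252 | +0.0239 |
| 0.3 to 0.7 | 8 v 16 | −0.0409 | +0.0298 |
| 0.5 to 0.8 | 12 v 16 | −0.0227 | +0.0099 |
| 0.5 to 0.8 | 12 v 20 | −0.0383 | +0.0180 |
| 0.5 to 0.8 | 8 v 16 | −0.0592 | +0.0226 |
| 0.6 to 0.9 | 12 v 16 | −0.0271 | +0.0100 |
| 0.6 to 0.9 | 12 v 20 | −0.0457 | +0.0181 |
| 0.6 to 0.9 | 8 v 16 | −0.0691 | +0.0225 |

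The sign differs between the two columns in all nine scenarios.

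**Does dividing by observed time solve it?** In part. In the same scenarios the difference in mean utility becomes +0.008 to +0.020, so the reversal goes. But with u0 = 0.5 and uh = 0.8, healing at week 12 and healing at week 20 both score 0.65: time spent healed earns no credit.

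**The case against.** The strongest reply is that the article never equates the QALY with the final-visit AUC. The Cost effectiveness section treats QALYs separately, and its closing 6-month label can govern the whole list, which would be the fixed horizon asked for here. It draws resource use partly from medical records, which need not end at a trial visit. Time to recurrence is also a planned outcome, so some information after healing is expected. The paper summarises a longer protocol, and QALY method is often left to fuller plans.

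Most of this stands. A reader might infer that QALYs and costs are cut off at healing and that the cost per QALY will take the wrong sign; the documents do not say so. Nor does the article's silence on covariates in the AUC model show that baseline adjustment is absent: its linear regression sentence extends adjusted models to other continuous secondary outcomes and may cover the AUC.

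Two things remain. The AUC window is stated, not omitted, and it is the wrong window for an unstandardised comparison. And a 6-month QALY horizon needs utilities that the schedule does not collect from healed participants, so a rule for them is needed on either reading.

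**Conclusion.** The concern holds for the final-visit EQ-5D AUC. Its length depends on the outcome, and with positive utilities an unstandardised version is biased against the faster-healing arm. A QALY built on it inherits the bias unless utility is extended to 6 months.

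The direction follows from the formula. The size, about −0.02 to −0.07 QALY stopped at healing against +0.01 to +0.03 over 26 weeks, rests on assumed utilities and healing times and on an AUC that is not divided by time.

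The 6-week EQ-5D AUC is not the concern, since its window is common except for anyone healed before week 6. Nor is pain, which is recorded in a diary fixed to the first 6 weeks. The primary outcome, the sample size and the time-to-healing analysis are untouched. Severity is moderate: these are secondary outcomes, though they bear on the economic question.

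**What to change.** - Compute the final EQ-5D AUC and the QALYs over one 26-week window from randomisation for every participant.
- For those healed earlier, carry the utility at healing forward to week 26.
- Add a sensitivity analysis that lowers the carried utility from the date of any recorded recurrence.
- State that the model adjusts for the baseline EQ-5D already collected.
- Confirm that costs use the same 26-week window, with resource use taken from medical records after healing.

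The cost is a few lines in the analysis and health-economics plans, with no change to visits. The downside is an explicit carry-forward assumption, which may overstate utility after an unrecorded recurrence. One EQ-5D at 6 months from early healers would replace that assumption with data, at the price of an extra questionnaire; the fix does not depend on it.
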